# SUMMARY

| Full title | Early and comprehensivecare bundle in elderly for acute heart failure: the ELISABETH stepped wedge cluster randomized trial |
| --- | --- |
| Acronym | Elisabeth |
| Coordinating Investigator | [name] |
| Scientific Director (if applicable) | [name] |
| Sponsor | Assistance Publique-Hôpitaux de Paris |
| Scientific justification | Acute heart failure (AHF) is one of the most common diagnoses for elderly patients in the emergency department (ED), with an admission rate higher than 80% and 1-month mortality around 10%. There is scarce evidence of any clinical added value of a specific treatment to improve outcomes, and European guidelines for the management of AHF are based on moderate levels of evidence, due to the lack of randomized controlled trials.  Recent reports suggest that the very early administration of full recommended therapy may decrease mortality. However, several studies highlighted that elderly patients often received suboptimal treatment: For example, less than a third of them received nitrates therapy while it is recommended. Furthermore, a recent preliminary study reported that only 50% of them are assessed for precipitating factors – although it has been reported that precipitating factors are independently associated with mortality.  Our hypothesis is that an early care bundle that comprises early and comprehensive management of symptoms, along with prompt detection and treatment of precipitating factors should improve AHF outcome in elderly patients. |
| Main objective and primary endpoint | Compare the efficacy of an early and comprehensive strategy in AHF elderly patients to the usual care on morbidity and mortality at 30 days.  Primary endpoint: number of days alive and out of hospital at 30 days after ED visit.  The experts of the European Society of Cardiology has recently considered this endpoint as relevant and adapted (see p. 13). |
| Secondary objectives and endpoints | To evaluate the effect of AHF management on early  morbidity and mortality.  Secondary endpoints:  • 30-day cardiovascular death  • 30-day all causes death  • Hospital readmission at 30 days  • Length of stay in hospital  • Changes of more than 2 fold in creatinine level from inclusion to day 30 or to discharge whichever comes first. |
| Design of the study | Stepped wedge randomised trial (see p. 14)  The 15 participating centers will first be assigned to the “control period” for 4 weeks. Then, every 2 weeks, one center will be randomized to switch to the “intervention period”. After 32 weeks, all centers will then be in the “intervention group” for the last 4-week period of the trial. |
| Population of study participants | Patients aged ≥75 years |
| Inclusion criteria | Patients aged 75 years and older admitted to the emergency department with a diagnosis of AHF determined by the emergency physician, based on the presence of:   - at least one of the following symptoms : acute, or worsening of dyspnea, orthopnea - One or more of the followings: pulmonary rales, peripheral edema, a chest radiograph or transthoracic echocardiography showing pulmonary vascular congestion signs, increased natriuretic peptides (BNP or NT-pro-BNP). - Patients affiliated to French social security (“AME excepted”) - Written informed consent signed by the patient / the trustworthy person / family member / close relative, or inclusion in case of emergency and written informed consent will been signed by the patient (if need be by trustworthy person, family member or close relative) as soon as possible(article L1122-1-2 of the French Public Health Code) |
| Exclusion criteria | Patients are excluded if they have any of the followings:   - other obvious cause of acute illness (severe sepsis, ST elevation Myocardial infarction) - systolic blood pressure less than 100mmHg - severe mitral or aortic stenosis, or severe aortic regurgitation - known chronic kidney injury on dialysis - Time from ED entrance to inclusion > 6h - Patient under legal protection measure (tutorship or curatorship) and patient deprived of freedom |
| Interventions or product under investigation | NA |
| Comparator arm | NA |
| Other interventions added by the study | The intervention will not test any particular drug or medical disposal, but rather the application of the international guidelines (ESC, EUSEM, AHA) through the implementation of a protocol of care. The care bundle of early care with a checklist that includes the following checklist:   - Detection and treatment of AHF precipitating factors (infection, acute coronary syndrome or atrial fibrillation) - Treatment of congestion, including a protocol of nitrates titration, and low dose furosemide, as recommended by international guidelines - Non-invasive ventilation if indicated, as recommended by international guidelines - Preventive low molecular weight heparin, as recommended by international guidelines   During the control period, the standard of care will be treatment as usual, left at the discretion of the treating emergency physician |
| Expected benefits for the participants and for society | We anticipate a reduction in length of hospitalisation and rate of readmission. The intervention is aimed at increasing the number of days alive and at home in the first month after inclusion. This benefit for the patient should be associated with a reduction in the allocation of hospital resource. |
| Minimal risks and constraints added by the study | Minimal risk, as only recommended treatments will be administered  The intervention will not test any particular drug or medical disposal, but rather the application of the international guidelines (ESC, EUSEM, AHA) through the implementation of a protocol of care.  Validated treatment will be randomly attributed to a group of patients (List of interventions listed in the article L1122-1-2 of the French Public Health Code, and corresponding to a Minimal risks and constraints) |
| Scope of the study | Emergency care and acute heart failure |
| Number of participants included | 500patients |
| Number of sites | 15 centers in France  If one center withdraw from the trial before its start, we will invite another ED to participate (2 centers are listed as willing to participate if possible) |
| Schedule for the study | - inclusion period: 36 weeks - participation period (treatment + follow-up): 30 days - total duration: 36 weeks and 30 days |
| Number of enrolments expected per site and per month | 4 |
| Statistical analysis | No interim analysis is planned. Analysis will be performed at the end of the study after data review and freezing of data base according to ITT principle and with regard to cluster level randomisation. |
| Sources of monetary support | French ministry of health |

# SCIENTIFIC JUSTIFICATION FOR THE RESEARCH

## CURRENT KNOWLEDGE

Acute heart failure (AHF) is a syndrome defined as new-onset or worsening of symptoms and signs of HF,often requiring rapid escalation of therapy and hospital admission. The clinical presentation of AHF typically includes symptoms or signs related to congestion and volume overload rather than to hypoperfusion.^1^ Acute heart failure represents 5% of all emergency hospitalizations, and is the most common primary diagnosis in patients ≥75 years visiting the ED.^2,3^ The ED are the main entry to the hospital for AHF, with 64% of these admissions being subsequent to an ED visit.^4^ This syndrome is reportedly associated with poor outcomes, with a 80% rate of hospital admission, a median length of hospital stay of 10 days and a mortality around 10% at 30 days, and a readmission rate of 25-30% at 30 days.^5–7^

Despite a high rate of morbidity and mortality, the management of AHF has not changed for several decades and most clinical studies failed to demonstrate a positive impact of new drugs on patients’ prognosis.^8,9^European guidelines include the use of diuretics, nitrates, oxygen and non-invasive ventilation (NIV) when indicated along with the treatment of any potential AHF triggers (precipitating factors).However, these guidelines are based on moderate levels of evidence (IB and IIaB), and high-quality randomized controlled trials data (RCT) are lacking.^10–12^

In 1998 and 2000, the two cornerstones trials of Cotter et al. provided evidences of benefits associated with early vasodilatator therapy with nitrates, although on a very small sample of patients (less than 200 in total).^13,14^ Since then, every prospective trial on AHF management failed to report a clinical significant improvement of outcomes. Equipoise remains on many questions regarding the recommended therapeutics: the optimum dose and route of administration of diuretics are not clear, the use of nitrates is also debated, and the benefit of non-invasive ventilation (NIV) is unclear.^15–17^

Despite these controversies, recommendations and guidelines are published by international society (ESC, AHA, …) and constitute the basis of our understanding and standard of care.^10,11^ However, a large proportion of elderly patients in AHF do not receive adequate care, including low rate (30-50%) of nitrates therapy.^7,18,19^

In preparation of this grant application, we conducted a preliminary analysis in 8 French EDs participating in the present ELISABETH trial. For a 7-day period, we evaluated all consecutive patients aged 75 years and older with a diagnosis of AHF in the ED. Among the 73 consecutive AHF patients, 23 patients (32%) had not been investigated for the findings of precipitating factors of AHF (namely infection, acute coronary syndrome or atrial fibrillation). Moreover, among the 50 other patients for whom precipitating factors of AHF were investigated, 17 (one third) showed evidence of precipitating factors that were not subsequently treated in the ED, although diagnosed. Regarding nitrates therapy, only 25 out of the 73 included patients received recommended treatment. In total, only 18 elderly ED patients (23%) were managed according to the existing guidelines ([name] et al. 2017 manuscript under preparation).

The lack of solid evidence regarding the efficacy of full recommended therapeutic management of AHFS on outcomes may have been caused by four major shortcomings that we will address in the present ELISABETH trial:

1) The previous RCTs did not include in their protocol of care the systematic early assessment for precipitating factors, and subsequent treatment.^8,15,20,21^ The main reported triggers are acute coronary syndrome (ACS), infection, and atrial fibrillation.^22,23^ As the outcomes of AHF patient has been linked with the triggering factor, we make the hypothesis that early and comprehensive look up and treatment of these precipitating factors may improve the prognosis.^24^ A secondary analysis of the Arrigo et al. study showed that among the 15% of AHF patients with ACS, the administration of antiplatelet was associated with decreased mortality (11.4% vs 16.7%).^24^ Similarly, it is well established that the early introduction of antibiotics improve prognosis of infected patients.^25^ Along with administration of recommended treatment within the first hours of ED care, our trial will evaluate the impact of an algorithm for early detection and treatment of precipitating factors that may have contributed to the decompensation of the patient.

2) The previous RCTs only assessed the impact of single drugs, and not of a comprehensive care bundle.^8,9,15,20^ Due to polyfactorial causes of poor outcomes in elderly patients with AHF, we believe that an intervention that focuses only on the administration of a single drug may have a lesser effect than a care bundle. In the light of the high rate of sub-optimal care provided to elderly AHF patients, the inclusion of all aspect of the treatment seems mandatory to evaluate a therapeutic approach. To our knowledge, an intervention combining an early and multifaceted approach for AHF in the ED has never been studied.

3) The delay between ED arrival and randomization may have been too long: in recent large RCTs, this timeframe varied from 6 to > 24 hours.^8,20^ It has however been suggested that the introduction of decongestion treatment within hours in the ED is associated with better outcomes.^26,27^ Furthermore, a recent prospective study reported that early decongestion treatment with diuretics in the first hour was an independent predictor of improved in-hospital survival (Odds Ratio OR 0.39, [0.20-0.76]) ^28^.

In the present study, nitrates and loop diuretics will be given within 1 hours of first medical contact in the ED.

4) Although elderly are described to most suffer of AHF, with worse outcomes, specific RCT in this frail population are lacking (ex. the recent True-AHF RCT, which evaluated the effect of ularitide infusion, excluded elderly patients).^8^ Thus our trial, focused on old AHFS patients, will be to the best of our knowledge the first to evaluate the impact of an early intensive approach in this target population.

## Hypotheses for the research

In elderly patients (≥75 years), acute heart failure (AHF) is associated with a high 30-day mortality and readmission rate. We hypothesis that a care bundle, which comprises very early and aggressive decongestion treatment along with assessment and treatment of precipitating factors will improve early outcomes for elderly patients that visits the ED with AHF.

## Description of the population of research participants and justification for the choice of participants

Patients with AHF, aged 75 years and older, admitted to the ED.
We chose to focus on elderly patients for several reasons:

- These patients have higher mortality rates due to frequent co-existing illness and comorbidities.^3,4^
- Elderly patients are quite an homogenous population. They share a similarity in AHF profile, with a predominant proportion of patients with preserved ejection fraction, and similar profiles of triggers (infection in most of the cases). By contrast to younger patients (< 75 years) in AHF, who are often patients with poor left ventricular ejection fraction and require a different care pathway, mostly based on decongestion treatment, especially diuretics.^5,29^
- Elderly patients are under-represented in clinical trials, and scientific evidence is often lacking, the diagnosis and management of AHF in this population is challenging.
- Elderly patients have been extensively shown to be undertreated, whilst this population would benefit as well as patients under 75.

## Interventions and products which will be performed or used as standard

No specific drug or medical disposal will be investigated *per se*. The present trial will evaluate the efficacy of administration of full optimaltherapy (being furosemide, isosorbidedinitrate, LMWH, antibiotics, antiplatelets…) as recommended by current guidelines See section 6 below.

## Interventions added for the research

The intervention will not test any particular drug or medical disposal, but rather the application of the international guidelines (ESC, EUSEM, AHA) through the implementation of a protocol of care. The care bundle of early care with a checklist that includes the following checklist:

- Detection and treatment of AHF precipitating factors (infection, acute coronary syndrome or atrial fibrillation)

Treatment of congestion, including a protocol of nitrates titration, and low dose furosemide, as recommended by international guidelines

- Non-invasive ventilation if indicated, as recommended by international guidelines
- Preventive low molecular weight heparin, as recommended by international guidelines

## Summary of the known and foreseeable benefits and risks for the participants

Despite a small improvement in outcomes of elderly admitted for AHF within the past decades, its morbidity and mortality remains severe with a 10% rate of 30-day mortality, and 25-30% of early readmission rate.^6,7,18,29^ In the majority of cases, treatment can be initiated in the ED. However, many studies showed that a majority of these patients are still not getting recommended therapies in the ED – either for AHF *per se*, or for precipitating factors of AHF, especially acute coronary syndrome or infection.^7,16,18^

In this context, there is an urgent need of multidisciplinary management program of patients with AHF in the ED and following ED to ensure better results and adherence.^30^The great outcome improvement provided by early treatment in the ED have long been established in other settings (e.g., sepsis, myocardial infarction). Unfortunately, AHF has not been considered with this regard until recently. Some reports suggest the importance of time to introduce therapy in AHF. Data derived from ADHERE registry indicate that early treatment (<6h) in emergency departments would bear a positive impact by decreasing in-hospital mortality and morbidity rates (unadjusted OR for in-hospital mortality 0.77, adjusted OR 0.87 (95%CI [0.76 – 0.96]).^26^ Very recently, in their large prospective observational study, Matsue et al. reported a significant decreased mortality of AHF following the initiation of decongestion therapy within 1 hour in the ED (OR for in-hospital mortality of 0.39 (IC 95% [0.20-0.76]).^28^

As expressed by Januzzi and Felker in a recent editorial “***the failure of novel therapies for AHF requires us to make better use of what we already have. A systematic approach would allow an optimal management of acute HF, and in turn could finally improve outcomes.”***^31^If our hypothesis is confirmed, our trial of early intensive care bundle will be the first RCT showing a significant reduction in short term morbidity and mortality in elderly AHF, similarly to what was achieved for sepsis (with a 15% absolute reduction of in-hospital mortality).^32,33^

Lastly, it can be stressed that the observed high rate of deviation to the guidelines may be caused in part by their low level of evidence of these last one. A positive outcome of the execution of a care bundle based on these recommendations would increase physician’s adherence, and patients’ outcomes.

# OBJECTIVES OF THE RESEARCH

## Main objective of the research

To compare the efficacy of an early and comprehensive management strategy of AHF in elderly patients to the usual care on morbi-mortality at 30 days.

## Secondary objectives

To evaluate the effect of AHF management on early morbidity and mortality.

# Description of the research

## Primary endpoint

Our primary endpoint is:

**The number of days alive and out of hospital at 30 days after ED visit.**

This endpoint is considered as relevant by the group of experts of the European Society of Cardiology.^34^ In their consensus paper, the experts stated that although mortality should be captured, repeated hospitalizations should also be recorded. Especially in elderly patients, where the rate of readmission to the ED and rehospitalisation is elevated: up to 40% of heart failure admissions to the hospital are actually repeated admission for recurrence of symptoms within 30 days of a previous AHF event. ^3,6^

As expressed by Zannad et al.: “Despite their importance, repeat events are ignored in the majority of clinical trials, […], The ‘days alive and out of hospital’ endpoint incorporates the components of days in hospital (including days of the index hospitalization and repeat hospitalizations), days alive and not in hospital, and days dead into a single measure over a defined time frame (e.g. 30 or 60 days). This endpoint was developed to address the issue of repeat hospitalizations for all causes.” ^35–37^

This endpoint also makes it possible to obtain information which could have some benefits from an health-economic point of view.^34^ Furthermore, this endpoint was reported to better capture the burden of mortality and hospital stay during the follow up period. As expressed by Allen et al., this endpoint has the advantage to combine mortality, length of stay, and burden of subsequent hospital stay into a single endpoint, and therefore is appropriate to capture morbidity and mortality.^38^

Lastly, the timeframe of 30 days is recommended as a shorter timeframe would not catch recurrence and morbidity, and a longer timeframe would catch events that are more likely linked to chronic morbidity of the patients than to the AHF syndrome.^24,34,38^

## Secondary endpoints

- 30 day all-cause mortality
- 30 day cardio-vascular mortality
- Hospital readmission at 30 days
- Length of in hospital stay truncated at 30 days
- Changes of more than 2 fold in creatinine level from inclusionto day 30 or to discharge whichever comes first.

Creatinine will be measured at day 0 in the ED, and at discharge day or day30, whichever comes first.

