### Research end date (D30)

The end of study visit will be at 30 day. The in-hospital mortality will be truncated at 30 days.

- If the patient is still hospitalized: the follow-up visit will consist of a hospital visit and a chart review to ascertain the primary endpoint.
- If the patient is not still hospitalized: the follow-up visit will consist of a phone interview topatient/ trustworthy person / family member / close relative. The family practitioner of the patients will be sought for information in case the patients/relatives cannot be reached.

If follow up is impossible, the investigators or CRT will contact the city hall and administrative service of his hometown to seek for possible death.

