## Expected length of participation, chronology and duration of the study

The maximum duration between ED arrival and enrolment will be 6 hours.

After inclusion; the care bundle (treatment period) should be completed within 4 hours.

In both periods, each subject will participate in the study for 30 days (see above).

As shown in figure 1, there will be a first period of 4 weeks where all centres will be in the control arm, then every 2 weeks one centre will change arm and switch to the “intervention” phase. After a total of 32 weeks, all centers will be in the “intervention” arm, for four more weeks. The total duration of recruitment will therefore be 36 weeks.
Since patients will be followed until 30 days, the total duration of the study will then be of 36 weeks and 30 days.

|  |  |  |
| --- | --- | --- |
| Maximum period between D0 and enrolment  Length of Inclusion period |  | 6 hours  36 weeks |
| Duration of participation for each subject, of which: |  |  |
| - protocol period: |  | 4 hours |
| - Follow-up period: |  | 30 days |
| Total study duration: |  | 36 weeks and 30 days |

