# EFFICACY ASSESSMENt

## Description of parameters for assessing efficacy endpoints

The primary endpoint (days alive and out of hospital at day 30) will be measured at the end of the 30 days follow up period, either by hospital visit, phone interview, and medical chart review. Vital status, date of death and date of discharge will be collected.

A death during the follow up period will correspond to 0. An ED visit will correspond to “one day” at the hospital.

For example, a patient not admitted (at day 0), with no return visit to the hospital, and alive at day 30 will have 30 days alive and out of hospital.

A patient who is admitted (at day 0) and stays 8 days in the hospital before being discharged and have no readmission and no return visit to the ED would have a “22 days alive and out of hospital at 30 days”.

A patient that is admitted and die at 13 days, either at home or in hospital will have 0.

A patient that is admitted for 10 days, discharged home for 5 days then admitted at day 16 for 15 days will have 5 days alive and out of hospital (namely day 11, 12, 13, 14 and 15).

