## Secondary evaluation criteria

In hospital mortality, all causes mortality at 30 days and cardiovascular mortality at 30 days will be compared between groups by using Pearson's chi-square test or Fisher exact test.

If possible, generalized linear regression mixed model with Poisson distribution will be performed. If the number of events is sufficient, generalized linear regression mixed model using logit link will be performed.

The length of stay in hospital in days will be compared between the two periods by using Student t-test or Wilcoxon rank-sum test as needed. If possible, a linear regression mixed model will be performed. A random effect for each cluster will be considered and considered fixed effects will be: strategy and, for the stepped wedge design, time representing each step. In case of non-normality distribution of the interest variable, a transformation could be realized.

Percentage of patients with a change of more than 2 fold in creatinine between inclusion and 30 days will be compared between groups by using Pearson's chi-square test or Fisher exact test. If possible, generalized linear regression mixed model with Poisson distribution will be performed. If the number of events is sufficient, generalized linear regression mixed model using logit link will be performed.

Second analysis will be performed on the per protocol population.

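### Length of stay is compared as days truncated at 30 with no place for in-hospital death, and readmission is a listed endpoint that Section 13.3 does not analyse

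*Protocol*

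**What the plan says.** **Length of stay.** Protocol Section 4.2 defines the endpoint as "Length of in hospital stay truncated at 30 days". Section 13.3 states: "The length of stay in hospital in days will be compared between the two periods by using Student t-test or Wilcoxon rank-sum test". It adds, if possible, a linear mixed model with a random centre effect and fixed effects for strategy and step. Truncation is the only scoring rule given.

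**Death.** Section 9.1 states "A death during the follow up period will correspond to 0", and Section 13.2 repeats it. In both places the rule belongs to days alive and out of hospital. It is not extended to length of stay.

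**Readmission.** Section 4.2 lists "Hospital readmission at 30 days" without a time origin. Section 6.2 says "In both periods, each subject will participate in the study for 30 days", and the Research end date (D30) subsection of 6.1 says "The end of study visit will be at 30 day". Events can therefore be counted only up to day 30 from the ED visit.

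**Analysis list.** Section 13.3 covers in-hospital mortality, all-cause and cardiovascular mortality at 30 days, length of stay and creatinine. Readmission is absent. In-hospital mortality is present but is not among the endpoints of Section 4.2 or the Summary. Section 9.2, on collecting the efficacy data, has the same mismatch.

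**Expected benefit.** The Summary says: "We anticipate a reduction in length of hospitalisation and rate of readmission".

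**The concern.** A stay can end by leaving alive or by dying. A comparison of days treats the two alike, although one is the aim of care and the other its failure. With 30-day mortality of about 10% (Section 2.1), enough patients may die in hospital to move the comparison, and the direction is awkward: preventing early deaths lengthens the mean stay.

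Readmission has a related feature. A patient can be readmitted only after leaving alive, so within a window fixed at the ED visit a shorter index stay means more days at risk. Some of any benefit on readmission would be masked by the shorter stay that the sponsor also expects.

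At stake is the reading of two secondary endpoints that the Summary names as anticipated benefits. There is also a plain mismatch between the endpoint list and the analysis list.

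**Working it through.** **The plan's own figures.** The protocol gives no target for length of stay or readmission. Its only calculation (Section 13.4) is for the primary endpoint: 4 × (9 × (1.960 + 0.842) / 3)² = 282.6, against 283 stated; 283 × 1.609 = 455, against 454 stated; 454 × 1.1 = 499.4, against 500 stated. It reproduces, and this point does not touch it.

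**Length of stay**

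Inputs from Section 2.1: median stay 10 days, mortality about 10%. Assumptions: mean stay S = 10 days in survivors (the document gives a median), all deaths in hospital, death on day d = 3 to 7, and mortality changing from p₀ = 10% to p₁ = 5%.

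Mean stay when the stay ends at death = (1 − p) × S + p × d. The difference, bundle minus control, is (p₀ − p₁) × (S − d).

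| Day of death | Mean at 10% mortality | Mean at 5% | Difference |
|---|---|---|---|
| 3 | 9.30 | 9.65 | +0.35 |
| 5 | 9.50 | 9.75 | +0.25 |
| 7 | 9.70 | 9.85 | +0.15 |

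If mortality rose to 15%, the same amounts would appear as a shorter stay. The shift vanishes at d = S and reverses for later deaths.

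If deaths are instead scored as 30 days, the means are 0.90 × 10 + 0.10 × 30 = 12.0 and 0.95 × 10 + 0.05 × 30 = 11.0, a difference of −1.0 day. The scoring of death therefore decides the sign.

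**Readmission**

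Inputs: 25 to 30% readmitted at 30 days and a stay of 10 days (Section 2.1). Assumptions: this rate is counted from the ED visit (the document gives no origin), the daily hazard after discharge is constant, the stay is the same for all patients, and the bundle shortens it by 1 to 3 days without changing the hazard.

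h = −ln(1 − r) / (30 − 10), and the new proportion is 1 − exp(−h × (30 − new stay)).

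| New stay | From 25% | From 30% | Hazard cut needed to break even |
|---|---|---|---|
| 9 days | 26.1% | 31.2% | 1 − 20/21 = 4.8% |
| 8 days | 27.1% | 32.5% | 1 − 20/22 = 9.1% |
| 7 days | 28.2% | 33.7% | 1 − 20/23 = 13.0% |

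With 227 patients per group (454 / 2), ignoring clustering, shifts of this size have about a 5 to 13% chance of reaching significance.

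A sign change is possible. With a true 10% hazard reduction and a 7-day stay, the fixed window gives 1 − exp(−0.9 × 23h) = 25.8% against 25.0%. Thirty days counted from discharge would give 32.2% against 35.0%.

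**The case against.** **The protocol never says that a death is a short stay.** This is correct. A reader might infer that it adopts this scoring, but it only leaves death unaddressed, and a SAP not shown here could set a rule. What remains is that the protocol fixes the form of the analysis: days, compared by tests or a linear model that cannot separate live discharge from death. A SAP rule within that form only chooses which way deaths push the result.

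**The misreading is guarded against.** This largely stands. The primary endpoint, "The number of days alive and out of hospital at 30 days after ED visit", combines death, index stay and readmission, and 30-day mortality is reported beside length of stay. The Summary states the aim of the intervention in terms of days alive and at home, so these two secondary endpoints do not carry the main claim alone.

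**Readmission by day 30 in all included patients is a legitimate intention-to-treat quantity.** This stands, and it is a reason to keep it. An analysis from discharge, or with a days-at-risk offset, conditions on live discharge, which occurs after allocation and may itself be affected by the bundle.

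**A larger readmission effect might be inferred from the sample-size target.** Using 14 and 17 days alive and out of hospital as time at risk would take 25% to 29.5% and 30% to 35.2%. The documents do not support that step. The score sets every death to 0, subtracts days of readmission and includes days after a first readmission, so it is not time at risk of first readmission.

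**Conclusion.** The point holds as a matter of interpreting secondary endpoints. The planned comparison of length of stay does not distinguish leaving alive from dying. If the stay ends at death, a 5-point fall in mortality makes the mean stay look 0.15 to 0.35 day longer, given a 10-day mean in survivors and deaths in hospital at day 3 to 7. The fixed readmission window adds about 1 to 4 percentage points when the stay is 1 to 3 days shorter at constant hazard. Both shifts are modest, and the readmission shift would seldom be significant in a trial of this size.

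A reader might conclude that an effective bundle will look harmful on readmission. That requires the fall in daily hazard to be smaller than the break-even values above, whereas the sponsor expects readmission to fall, so it is a possibility and not a prediction.

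The mismatch between Sections 4.2 and 13.3 rests on no assumption. The primary endpoint and its sample size are not affected.

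**What to change.** 1. **Length of stay.** Analyse time from the ED visit to live discharge, up to day 30, with in-hospital death as a competing event and with centre and step in the model. Keep crude days in hospital as a descriptive measure of resource use.
2. **Readmission.** State that the window runs from the ED visit to day 30. Keep the proportion of all included patients readmitted in it, and add an analysis to Section 13.3 with death as a competing event and with centre and step in the model. Beside it, as supportive, report the first-readmission rate per day at risk after live discharge, counting days only up to the first readmission, and note that this conditions on live discharge.
3. **Lists.** Reconcile Section 13.3 (and Section 9.2) with Section 4.2: add readmission to the analyses, and either list in-hospital mortality as an endpoint or remove its test.

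The cost is protocol wording and a little more analysis work. Sections 9.1 and 13.2 already require the admission, discharge and death dates for the primary endpoint, so no new data are needed.
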